## Abstract

**Background:**

Exercise related leg pain (ERLP) is a common lower limb overuse injury characterised by pain located between the knee and ankle that occurs during activity. The high incidence of the condition, subsequent interference with participation in physical activity and substantial recovery time, highlights a need for effective interventions. Whilst many interventions have been described for the management of ERLP, currently there is a lack of high quality evidence for an effective intervention for the condition.

**Methods/Design:**

A single-blinded randomised controlled clinical trial will be conducted in a community setting. Forty-five female volunteers aged between 18 and 40 years with a history of insidious onset of pain located between the knee and ankle of at least one month duration that is aggravated by weight bearing activities will be recruited for the study. Suitable participants will be randomly allocated to one of three treatment groups for the 6 week intervention period: (i) exercise only, (ii) rigid anti-pronation tape and exercise, (iii) elastic anti-pronation tape and exercise. Outcomes will be measured at baseline, 1, 2 and 6 weeks using primary outcome measures of usual and worst pain visual analogue scale and global perceived improvement. Secondary outcome measures will include Foot and Ankle Ability Measure, Patient Specific Functional Scale and amount of activity in the previous week. In addition, participants will be contacted by phone to obtain primary and secondary outcome measures at 12, 18, 24 and 30 weeks.

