### Outcome measurements

A blinded assessor will perform tests of foot mobility and other outcome measurements at baseline and then at follow-up sessions occurring at 1, 2, and 6 weeks. Participants will also be contacted by email or phone to obtain questionnaire outcome measurements only at 12, 18, 24 and 30 weeks. At the completion of the test sessions, assessor blinding will be evaluated via a questionnaire.

Biomechanical effectiveness of the intervention will be evaluated by measuring vertical mobility of the midfoot. These measures will be performed at baseline and then at follow-up sessions occurring at 1, 2, and 6 weeks. In addition to these measurements by the assessor, the treating physiotherapist will also obtain a measurement of foot mobility before and after each application of tape to ensure consistency of application of the intervention. Measurement of vertical mobility of the midfoot will be performed using two custom made platforms and modified callipers with the participant in two positions (i) standing on both feet with equal weightbearing and, (ii) sitting with legs relaxed over the edge of a plinth. Dorsal arch height difference will be calculated by subtracting the dorsal arch height in standing from the dorsal arch height in non-weight bearing. This measurement has been described in detail previously and demonstrates high inter- and intra-rater reliability [15].

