### Planned statistical analysis

Data processing, data entry and data analysis will be performed by an assessor who is blinded to group allocation. The primary analysis of the data will be performed on an intention-to-treat basis. SPSS software (version 21.0) will be used for statistical procedures. Demographic data, clinical characteristics of pain and physical activity level at baseline will be examined for comparability across the three intervention groups. To evaluate the effect of the interventions on pain and function (VAS, FAAM, PSFS, Physical activity level) a two-way repeated measure analysis of variance with between subject factor of intervention group and within subject factor of test session, will be performed. Global perceived effect will be dichotomised to either success (completely recovered, much improved, improved) or no success (no change, worse, much worse) and expressed as relative risk reduction and numbers needed to treat. For all statistical procedures age, weight and height will be included as covariates and alpha level will be set at 0.05.

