## Discussion

This study will be the first randomised controlled trial to evaluate the effectiveness of anti-pronation taping and lower limb muscle training for ERLP. As there is currently a lack of evidence for effective interventions for ERLP [11], the results of this study will provide evidence to inform healthcare providers in the management of the condition. For example, if this study identifies one intervention to be superior to the others, this intervention can be recommended in preference to others. Alternatively, if no differences are identified between the three intervention groups, then taping would be considered to have no additional benefit over exercise alone and it would therefore be recommended that clinicians could focus on exercise alone rather than additional taping. An important feature of this study is the inclusion of a follow-up at 12, 18, 24 and 30 weeks. Accordingly, this study will provide an evaluation of both the short and long term effectiveness of an intervention for ERLP.

The three intervention groups evaluated in this study were selected to target a reported risk factor for the condition (increased foot mobility) as well as to reflect clinical practice. Clinical opinion pieces and review articles advocate the reduction of pain through “relative rest” (load modification, alternative training), NSAIDS and ice in the acute phase of ERLP, and following this, the commencement of strengthening exercises [1, 12, 13]. Therefore, we selected a lower limb muscle training intervention which consisted of advice and education on ERLP and load management, followed by strengthening exercises. For comparison, we included a combined intervention of taping and lower limb muscle training. This was selected to reflect a tissue stress model approach to management whereby the short term use of external devices (such as taping) is advocated to alleviate tissue stress and then followed by conventional physical therapy modalities such as muscle strengthening exercises [35, 36].

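### Three unranked primary outcomes share an unadjusted 0.05 with no primary time point or arm contrast, so the error rate for declaring one arm superior is not held at 5%

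*Protocol article*

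**What the plan says.** All references are to the protocol article.

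- **Abstract, Methods/Design.** Three arms are compared "using primary outcome measures of usual and worst pain visual analogue scale and global perceived improvement". None of the three outcomes is placed above the others.
- **Outcome measurements, and the abstract.** Assessments take place "at baseline and then at follow-up sessions occurring at 1, 2, and 6 weeks", and afterwards "participants will be contacted by phone to obtain primary and secondary outcome measures at 12, 18, 24 and 30 weeks". That makes 3 + 4 = 7 follow-ups.
- **Planned statistical analysis.** The pain scales and the other continuous measures each get "a two-way repeated measure analysis of variance with between subject factor of intervention group and within subject factor of test session". Global perceived effect is split into success and no success and "expressed as relative risk reduction and numbers needed to treat"; no significance test, arm pair or session is named for it. The section ends with one rule: "For all statistical procedures age, weight and height will be included as covariates and alpha level will be set at 0.05".
- **Discussion.** As an example of how the results could be used: "if this study identifies one intervention to be superior to the others, this intervention can be recommended in preference to others".

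The article names no primary session and no primary arm contrast. The two taping sections under Intervention state that tape is used in the first two weeks of the six-week intervention period and not in the last four.

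**The concern.** A claim that one arm is superior could rest on usual pain, worst pain or global perceived effect, on any pair of arms, and on any session or on all of them together. Each route carries its own 0.05. Unless one is fixed in advance, the overall chance of a false claim exceeds 5%, and the route can be chosen after the data are seen.

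The session also defines the question. A contrast at week 1 or 2 falls within the taping period. A contrast at week 6 or later asks what remains after tape has stopped. The answers may differ, and the plan does not say which one decides the trial.

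**Working it through.** **1. The plan's own figure.** Sample size considerations gives 10 per group for 20 mm, SD 12.7 mm, power 0.80 and alpha 0.05. The standardised difference is d = 20/12.7 = 1.575. The normal approximation n = 2(1.960 + 0.842)²/d² = 15.70/2.480 = 6.3 gives 7 per group. The two-sample t-test gives 7.42, so 8; a three-group one-way ANOVA gives about 27 in total, so 9. Ten is therefore sufficient for pain. The t-test at 0.05/3 gives 9.996, which happens to round to 10, but the article states 0.05, so no adjustment can be inferred.

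**2. Counting the routes.** Three arms give 3 pairs. Three outcomes × 3 pairs = 9 comparisons at one session; × 7 follow-ups = 63. Global perceived effect alone has 3 × 7 = 21. The tests that the plan states are fewer: one ANOVA for each of the two pain scales, each with a group-by-session test and a group main effect.

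**3. False-positive rates with identical arms.** For k independent tests the rate is 1 − 0.95^k. Because the outcomes are correlated, the rates were also simulated. The settings were 2,000 trials each, 10 or 15 per group, eight sessions including baseline, Greenhouse-Geisser-corrected ANOVA, pairwise t-tests, and pairwise two-proportion tests for global perceived effect. All tests were two-sided, without covariates. The article gives no correlations or success rate, so these are assumptions: 0.3–0.9 between sessions, 0.3–0.8 between outcomes, success rate 60%. The Monte Carlo standard error is at most √(0.25/2000) = 1.1 percentage points.

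| Comparisons read | k | Independent | Simulated, any p < 0.05 |
|---|---|---|---|
| Two pain-scale group-by-session tests | 2 | 9.75% | 5–9% |
| The same plus two group main effects | 4 | 18.5% | 11–19% |
| Three outcomes × three pairs, one session | 9 | 37.0% | 23–29% |
| Two group-by-session tests plus 21 global-effect pairs | 23 | 69.3% | 34–59% |
| Every pair, outcome and session (hypothetical) | 63 | 96.1% | 48–90% |

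The upper ends of the first two rows come from a setting in which correlation decays over time. With constant correlation they are about 8% and 16%.

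**4. What counts as superior.** The Discussion speaks of one arm better than the others, which is stricter than any single p < 0.05. A second simulation used 4,000 trials, 15 per arm, outcome correlation 0.6–0.7 and between-session correlation 0.5–0.8. One arm was significantly better than both others:

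- somewhere among all 63 comparisons in about 12–21% of trials;
- at one session across the three outcomes in about 3–4%;
- for one outcome at one session in about 1.5%.

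**5. Does the remedy hold 5%?** Take one outcome, one session, an overall test at 0.05, and pairwise tests only if it is significant. If all three arms are equal, an error requires the overall test to reject, which happens 5% of the time. If exactly two are equal, only one true null pair is left and it is tested at 0.05. So the error is at most 5% for exactly three arms. The alternative of 0.05/3 = 0.0167 per pair gives t-test power for 20 mm, SD 12.7, of 80.0% at 10 per group and 95.5% at 15.

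**The case against.** The strongest reply is that the plan is narrower than the count of outcomes, arms and visits suggests. Each pain scale gets one repeated-measures ANOVA that uses all sessions and selects none. No pairwise or per-visit test is written down, and global perceived effect has no stated test at all. The recommendation sentence is an illustration in the Discussion, not a decision rule. Follow-up contrasts and their adjustment are details that an article may leave to an analysis plan.

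Most of this stands, and it limits the size of the point. A reader might infer that the plan runs 63 tests at 0.05 and that a false superior arm is therefore likely. The article does not support that: the 63 comparisons are not planned, and even if all were run, one arm would beat both others in only about 12–21% of null trials.

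Three things remain:

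- The 0.05 for every procedure and the three equal primary outcomes are stated choices, not omissions.
- A significant F test shows that the arms differ somehow, not which arm is better or when. A superiority conclusion needs contrasts, and the only rule given for them is 0.05.
- Relative risk reduction and number needed to treat are two-arm quantities, so this primary outcome cannot be reported without choosing pairs and sessions.

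**Conclusion.** The point holds as a lack of error control of moderate size. On the tests actually stated, the false-positive rate is about 5–9%, or 11–19% with group main effects. It reaches about 23–29% if the three outcomes and three pairs are read at one session. Higher figures apply only to comparisons that the plan does not list, and most of the events they count are a single p below 0.05 rather than one arm beating both others. Nothing in the article confines a superiority claim to the narrowest reading.

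That the rate is not held at 5% follows from the text. The percentages rest on assumed correlations, an assumed 60% success rate, two-sided tests and no covariates, and should be read as ranges.

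**What to change.** Name one primary outcome and one primary time point before any data are examined. One candidate is worst-pain VAS, since the entry criterion is set on worst pain, at 6 weeks, the end of the intervention period. Because tape is worn only in weeks 1–2, state that this choice asks about benefit after taping has ended; a week-2 time point would ask a different question.

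Test the overall three-arm difference at 0.05 and make the three pairwise comparisons only if it is significant, or use 0.0167 per pair. Treat usual pain, global perceived effect and all other sessions as secondary, reported with 95% confidence intervals. Tie any superiority recommendation to the primary test.

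The cost is wording, plus the loss of primary status for two outcomes. Power for pain on the plan's own inputs is kept with no extra participants. Keeping all three outcomes primary at one session would mean 0.05/9 per comparison. That needs 13 per group for 80% power (12.56 rounded up), so 15 − 13 = 2 dropouts per arm could be absorbed.

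The reassurance on power does not extend to the FAAM. With d = 9/26.7 = 0.337, the normal approximation gives 15.70/0.1136 = 138.2, so 139 per group; 10 per group gives about 11% power even at an unadjusted 0.05.

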**Discussion:**

This article describes a single-blinded randomised controlled clinical trial that will utilise high quality methodologies in accordance with CONSORT guidelines. The results of this study will contribute to the limited knowledge regarding effective interventions for the management of ERLP.

**Trial registration:**

Australian New Zealand Clinical Trials Registry (ACTRN12613000914763)

**Electronic supplementary material:**

The online version of this article (doi:10.1186/1471-2474-15-328) contains supplementary material, which is available to authorized users.

## Background

Exercise related leg pain (ERLP) is a lower limb overuse injury characterised by pain located between the knee and ankle that occurs during activity. The condition encompasses the clinical and pathological features of several commonly used labels such as shin splints, medial tibial stress syndrome, periostitis, stress fractures, tendinopathies and compartment syndrome [1]. ERLP is particularly common in running populations with 13 to 20% of running injuries presenting to sports medicine clinics attributed to ERLP [1]. Incidence of ERLP has also been reported to be higher in females than males [2–6]. Significant burden is associated with the condition with 40-60% of runners reporting that ERLP caused a reduction in running or an interruption to training [7, 8]. Furthermore, the condition is associated with lengthy recovery periods in both runners and military personnel [9, 10]. Given the high incidence of the condition, subsequent interference with participation in physical activity and substantial recovery time, effective interventions for management of ERLP are required.

Several interventions have been described for the management of ERLP such as load management, low-energy laser treatment, stretching exercises, strengthening exercises, compression stockings, leg braces, pulsed electromagnetic fields, ice massage, ultrasound, iontophoresis, phonophoresis, and extracorporeal shockwave therapy. Whilst many of these interventions have been investigated in the literature, a recent systematic review [11] has reported a lack of evidence for an effective intervention for the condition. Despite the lack of research evidence, there appears to be consensus among clinical opinion pieces and review articles for the use of “relative rest” (load modification, alternative training), NSAIDS and ice in the acute phase of ERLP [1], and following this, the commencement of strengthening exercises for the calf and intrinsic foot muscles as well as more proximal muscles including the abdominals and gluteals with the aim of improving endurance and running mechanics [1, 12, 13]. To further develop the evidence base from expert opinion and anecdotal reports, Winters and colleagues [11] have suggested that it may be important to first understand the aetiological factors contributing to the condition.

A systematic review and meta-analysis by Newman et al. [14] suggests that the aetiology of ERLP is likely multifactorial. The authors reported evidence for several contributing factors: previous history of the condition (relative risk (RR) 3.74), female gender (RR 1.71), decreased running experience (standardised mean difference (SMD) -0.74), higher body mass index (SMD 0.24), history of orthotic use (RR 2.31) and >10 mm vertical displacement of the navicular from a subtalar neutral position to bodyweight supported stance (RR 1.99), commonly termed “navicular drop” [15]. Of these factors however only body mass index and navicular drop are potentially modifiable. Based on these findings, it is conceivable that interventions which reduce body mass index or reduce navicular drop may have the potential to influence pain and function in individuals with ERLP.

Navicular drop provides an indication of the vertical mobility of the midfoot, which can also be measured by dorsal arch height difference [15]. Interventions which have demonstrated effectiveness in reducing vertical mobility of the midfoot include taping and exercise. Anti-pronation taping techniques, such as the low-Dye and augmented low-Dye (ALD), have consistently demonstrated reductions in vertical mobility of the midfoot and increased medial longitudinal arch height immediately following application, during walking and jogging, and following 20mins of jogging [16, 17]. Of interest, the ALD taping technique has also demonstrated maintenance of an increase in medial longitudinal arch height following removal of tape after two weeks of continual wear [18]. Importantly, these biomechanical effects have been demonstrated in ERLP populations [17–19], however the efficacy of the ALD in the management of pain and function has not been evaluated. These anti-pronation taping techniques have traditionally in the past been applied using a rigid (inelastic) sports tape, however in recent times, and at least since the 2008 Olympic Games, there has been increasing popularity in the use of elastic tapes, such as Kinesio tape™ , Dynamic Tape™, KT-Tape™, SpiderTech™ and Cure Tape™ [20]. The reasons underlying the increasing popularity of elastic taping are not known. The elastic nature of the tape and alternate fabrication with more waterproof materials may lead to increased comfort. It is also conceivable that the elastic recoil in the tape may provide mechanical assistance or resistance (deceleration or acceleration) to movement, therein reducing the load demands on musculotendinous units while also permitting full range of motion to occur. Nevertheless despite their growing utility in the clinical setting, no study to date has evaluated the efficacy of an elastic taping technique in the management of ERLP.

Plantar intrinsic foot muscle training consisting of submaximal flexion of the metatarsophalangeal and proximal interphalangeal joints to raise medial longitudinal arch height has also demonstrated reductions in vertical midfoot mobility. Mulligan et al. [21] reported that a four week program consisting of three minutes daily of this plantar intrinsic foot muscle exercise, which progressed from sitting to bilateral and single leg stance, produced a reduction in navicular drop. This reduction in navicular drop was evident at conclusion of the program and was maintained another four weeks following cessation of the program. This training program, however, was evaluated in an asymptomatic population and has not been investigated in individuals with ERLP. In addition, there is evidence that during functional tasks motion of the foot is related to more proximal motion at the hip, suggesting that a whole limb approach to control midfoot mobility may be warranted. Specifically, increased navicular drop has been reported to be related to increased hip internal rotation during a single-leg squat [22] and moderate to strong correlations have been reported between frontal and transverse plane movements of the hip and frontal plane movement of the foot during walking [23, 24]. This evidence suggests that strengthening exercises for the hip abductor and external rotator muscles may also have the potential to influence foot mobility, however this has not been investigated.

The current lack of evidence for effective interventions for the management of ERLP warrants the conduct of further high quality randomised controlled trials. A reasonable rationale for the development of an effective intervention may be one based on current clinical expert opinion and addressing identified risk factors for the condition. As previously discussed, there appears to be a general consensus that advocates relative rest followed by strengthening exercise(s) for the management of ERLP. Whilst several risk factors for the condition have been identified, foot mobility is one of two modifiable factors. Anti-pronation taping and plantar intrinsic foot muscle training have demonstrated the ability to reduce foot mobility, however, no scientific study has evaluated the effectiveness of either intervention in the management of pain and function in ERLP.

## Methods

### Aim

The aim of this project is to compare the effectiveness of (i) lower limb muscle training alone, (ii) lower limb muscle training and rigid anti-pronation taping, and (iii) lower limb muscle training and elastic anti-pronation taping, for the management of ERLP.

### Study design

A randomised controlled clinical trial will be conducted in a community setting over a 12 month period. The Australian Catholic University Human Research Ethics Committee has granted ethical approval and all participants will provide informed written consent prior to commencement in the trial. An individual independent to the trial will perform the computer-generated randomisation sequence and preparation of envelopes containing the group allocation. The physiotherapist will communicate with participants regarding group allocation; due to the nature of the intervention it will not be possible to blind the treating physiotherapist or the participants. An assessor blinded to group allocation will perform outcome measurements at all time points. Data entry and statistical analysis will be performed by a blinded assessor. Figure 1 provides an overview of the study protocol.

